## Abstract

**Background:**

The most appropriate time to initiate dialysis after surgical insertion of Tenckhoff catheters is not clear in the literature. There is the possibility of peritoneal dialysis (PD) complications such as leakage and infection if dialysis is started too soon after insertion. However, much morbidity and expense could be saved by reducing dependency on haemodialysis (HD) by earlier initiation of PD post catheter insertion. Previous studies are observational and mostly compare immediate with delayed use. The primary objective is to determine the safest and shortest time interval between surgical placement of a Tenckhoff catheter and starting PD.

**Methods/Design:**

This is a randomised controlled trial of patients who will start PD after insertion of Tenckhoff catheter at Royal Brisbane and Women's Hospital (RBWH) or Rockhampton Base Hospital (RBH) who meet the inclusion criteria. Patients will be stratified by site and diabetic status. The patients will be randomised to one of three treatment groups. Group 1 will start PD one week after Tenckhoff catheter insertion, group 2 at two weeks and group 3 at four weeks. Nurses and physicians will be blinded to the randomised allocation. The primary end point is the complication rate (leaks and infection) after initiation of PD.

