### Participants

Participants will be stratified by site and diabetic status. The patients will then be block randomised in equal proportions to the three treatment groups using randomly varying blocks of size three and six. The randomisation sequence was generated using Stata 11 software [15]. Group 1 will start dialysis one week after Tenckhoff catheter insertion, group 2 at two weeks and group 3 at four weeks. A research nurse independent of study nurses and physicians will undertake randomisation process.

Patients will initiate dialysis in equivalent fashion apart from the study variable of delay period before initiation. The patients will be trained by the PD nurses in their respective centres. The PD exit site and tunnel will be examined according to the usual clinical practice at each site to detect any complications. This will not interfere with routine dressing changes or reviews currently in practice.

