### Outcome measures

#### Primary

Peritoneal fluid leaks (over the four weeks following start up of PD) and/or PD related infection - either exit site and/or tunnel and/or peritonitis - over the four weeks following start up of PD (Table 1).

**Table 1 T1:** Explanation of definitions to be used as part of this study

Terms	Definitions
Dialysate leak [17]	Exit-Site leak: Appearance of any moisture around the PD catheter that can be identified as dialysate (leak that contains a high glucose concentration, documented by a positive glucose dipstick of the leaking fluid)
	Dialysate leaks include not only those occurring around catheter but also dialysate loss from the peritoneal cavity, except that via the lumen of the PD catheter. If the diagnosis is uncertain Tenckhoffogram (intraperitoneal infusion of contrast material through the catheter with computed tomography) performed to confirm the anatomical leak[18]

Peritonitis [19]	Presence of two clinical signs and symptoms:
	• abdominal pain, nausea, vomiting, diarrhoea, fever and cloudy dialysate
	• Peritoneal dialysate WCC > 100/mm^3 ^with 50% neutrophils
	• Demonstration of bacteria on gram stain or culture

Exit site Infection (ESI)	Presence of purulent discharge or two of three of the following: erythema of >13 mm, induration and tenderness. Exit- site swab will be obtained in all suspected cases of ESI.

Tunnel Infection	Presence of two of three of the following: induration, tenderness, and radiographic evidence of a collection along the PD catheter tunnel.

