### Data collection

Data will be obtained by history from the participant or extracted from the clinical notes. These include:

1. Participant information - age, gender, weight, height, allergies, cause of kidney disease, co-morbidities

2. Date of PD catheter insertion and start of this period of peritoneal dialysis

3. Type of PD catheter and the technique by which PD catheter was inserted

4. Previous dialysis history

5. PD related complications

6. HD related events

7. Laboratory investigations - full blood count, electrolytes, coagulation profile, liver function test and C-reactive protein at admission to hospital as part of usual care.

8. Microbiology results - Gram stain, culture and antimicrobial sensitivities of dialysate fluid at admission to hospital if there is clinical suspicion of peritonitis

9. Antibiotics and other drugs prescribed concomitantly

10. Length of stay in hospital.

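### The abstract says nurses and physicians are blinded, but the arm is the interval from catheter insertion to PD start, so treating staff can infer it once PD begins; the Methods support only concealed allocation

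*Protocol article*

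**What the plan says.** The abstract (Methods/Design) makes the only blinding statement in the article: "Nurses and physicians will be blinded to the randomised allocation".

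The body gives the following.

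- **Arms** (Participants): "Group 1 will start dialysis one week after Tenckhoff catheter insertion, group 2 at two weeks and group 3 at four weeks".
- **Randomisation** (Participants): "A research nurse independent of study nurses and physicians will undertake randomisation process".
- **Contact with patients** (Participants): "The patients will be trained by the PD nurses in their respective centres".
- **Detection of complications** (Participants): "The PD exit site and tunnel will be examined according to the usual clinical practice at each site to detect any complications".
- **Data source** (Data collection): "Data will be obtained by history from the participant or extracted from the clinical notes". The listed items include "Date of PD catheter insertion and start of this period of peritoneal dialysis".
- **Primary outcome** (Outcome measures, Primary): leak or PD-related infection in the four weeks after PD start. Table 1 defines exit-site infection as "Presence of purulent discharge or two of three of the following: erythema of >13 mm, induration and tenderness". Leak and peritonitis definitions also draw on dipstick, imaging, cell count, Gram stain and culture.

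**The concern.** A reader of the abstract would take the primary outcome as recorded by staff who did not know the arm. Here the treatment is itself a time interval, visible to anyone who knows the date of surgery and the date PD began.

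The Background gives staff a reason to expect a difference: it says leaks and infection can occur when PD starts too early. Staff with that expectation might examine, test or label more readily after an early start. Staff who favour early start might do the opposite. The first pushes a true non-inferiority result towards failure, and the second pushes a harmful early start towards a non-inferiority claim. At about 3% events per arm, a few labels carry the result.

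**Working it through.** **1. Can the blinding statement hold?** The arm is the insertion-to-start interval. Both dates are recorded, and the primary window cannot be applied without the start date. PD nurses train the patients. The Discussion says the Brisbane site currently waits four weeks, so a start at one or two weeks would stand out there. Bridging HD during a delay is also visible. After PD starts, therefore, staff caring for the patient can infer the arm. Before assignment, the independent research nurse protects the sequence. That is concealment, and it is not in question.

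**2. The plan's own figure.** Statistical considerations gives 105 per group for a 10-point margin, a 3% rate, 80% power and an overall one-sided alpha of 0.05 adjusted for multiple comparisons. It states neither the test nor the adjusted alpha. With variance restricted to the margin (Farrington-Manning), n = (z₁₋α√V₀ + z₀.₈√V₁)²/0.10², where V₀ = 0.1190 and V₁ = 2 × 0.03 × 0.97 = 0.0582. At α = 0.05/3 this gives 88, or 107 with a continuity correction. At α = 0.05/6 it gives 106. The unpooled Wald formula at 0.05/3 gives 52. So 105 is roughly reproducible, but by more than one route. For that reason the next step uses two tests and a range of alpha.

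**3. How many labels overturn the result?** Expected events per arm are 105 × 0.03 = 3.15, so take 3 in the four-week arm. For x events in an early arm, z = [0.10 − (x − 3)/105]/SE. For the Wald test, SE² = [p₁(1−p₁) + p₀(1−p₀)]/105 with observed proportions. The score test uses the proportions restricted to a 10-point difference.

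Example at x = 6: the difference is 3/105 = 2.86 points. Score SE is 0.0341, z = 0.0714/0.0341 = 2.10, one-sided p = 0.018. Wald SE is 0.0279, z = 2.56, p = 0.005. At α = 0.0167 the score test fails and the Wald test passes.

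| One-sided alpha (assumed) | Score: largest passing x | Extra events to fail | Wald: largest passing x | Extra events to fail |
|---|---|---|---|---|
| 0.0083 | 4 | 2 | 6 | 4 |
| 0.0167 | 5 | 3 | 6 | 4 |
| 0.025 | 6 | 4 | 7 | 5 |
| 0.05 | 7 | 5 | 8 | 6 |

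*Extra events* are counted beyond parity with 3. The range is two to six, or 2/105 = 1.9% to 6/105 = 5.7% of an arm.

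**4. Both directions, for scale.** These figures use an unpooled Wald test at 0.05/3 and assumed bias sizes.

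- *Over-recording in the early arm, true rates 3% and 3%:* power is 98% with no bias. It falls to 92%, 80%, 63% and 30% with 1, 2, 3 and 5 points of extra recording.
- *Under-recording in the early arm, true rates 13% and 3% (at the margin):* the chance of a false non-inferiority claim is 1.7% with no bias. It rises to 3.9%, 8.6% and 17.5% if 10%, 20% or 30% of early-arm events are missed.

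**The case against.** The strongest reply is that the article never says the staff who know the interval are the ones who classify the endpoint. It says PD nurses train patients, but not who starts PD. It says exit sites are examined under usual practice, but not by whom, and it names no one who abstracts the notes. A masked adjudicator could exist in the full protocol, and a condensed article need not mention one. All of this stands. A reader might infer that the same unmasked nurses and physicians judge every primary event. The document does not establish that, and the absence of an adjudication procedure is not itself the finding. A masked adjudicator would still not make the sentence about nurses and physicians true.

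Second, a reader might treat the whole endpoint as subjective. Table 1 does not support this. An exit-site leak is documented by glucose dipstick, with contrast CT when the diagnosis is uncertain. Peritonitis criteria include cell count and Gram stain or culture, and exit-site erythema has a 13 mm threshold. What remains exposed is mainly induration and tenderness at the exit site and tunnel, and the decision to test at all.

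Third, it is tempting to say that exactly three labels reverse the conclusion. That holds only for a score test at 0.0167, where six events miss narrowly (p = 0.018). The article states neither, and Data analysis names logistic regression. Only the range of two to six is defensible.

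**Conclusion.** The point holds in limited form. The abstract claims a protection that the design cannot give treating staff once PD starts, and the Methods describe concealment only. This is a property stated wrongly, not a detail left out. Randomisation is unaffected.

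That knowledge of the arm reaches the outcome classification is an inference, and the exposure is concentrated in the clinical signs and the decision to test. The consequence is material because events are few: about two to six extra early-arm labels overturn non-inferiority. That range assumes 3 events in the four-week arm, 105 per arm, an absolute 10-point margin, a score or unpooled Wald test, and one-sided alpha from 0.0083 to 0.05. Missed early-arm events push the other way, towards a false non-inferiority claim. The correction should be made, but the concern does not invalidate the trial.

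**What to change.** 1. Replace the blinding statement with: *allocation concealed until assignment; treating staff not blinded once PD starts*.
2. Prespecify a sensitivity analysis of the primary outcome limited to objectively documented Table 1 events:
   - leak confirmed by dipstick or imaging;
   - peritonitis with cell count, Gram stain or culture evidence;
   - purulent exit-site discharge;
   - tunnel infection with a radiographic collection.

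   A positive swab alone should not count. Table 1 asks for a swab in suspected cases but does not make a positive result diagnostic.
3. Where existing staff allow, have primary events classified from records with the insertion and PD start dates removed.

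**Cost:** a wording change and one further analysis, based on results that the Table 1 definitions already call for. Date-masked classification needs some staff time. The stated design will look less favourable. The sensitivity analysis does not remove bias in the decision to test, because a patient never dipsticked, cultured or imaged cannot become a confirmed event by those routes.

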**Discussion:**

The study will determine the most appropriate time to initiate PD after placement of a Tenckhoff catheter.

**Trial Registration:**

ACTRN12610000076077

## Background

Peritoneal dialysis (PD) catheters are inserted surgically or laparoscopically into the peritoneal cavity for the initiation of PD. The best time to use a PD catheter after its insertion is not clear from the literature. Complications such as dialysate fluid leaks and infection at the exit site or peritonitis can occur if PD is initiated too soon after insertion of the catheter [1]. Bridging hemodialysis (HD) may be required if PD is delayed [2]. Morbidity and expense could be saved by earlier initiation of PD post Tenckhoff catheter insertion that would limit the requirement for bridging HD. Current practice varies widely. Studies reported in this area have been observational and mostly compare immediate with delayed use[3,4]. Some studies support delayed use but do not test different delay intervals and can not tell us the optimal time to initiate PD [5-7]. Recent studies report a very low leak incidence after short break in period, attributed to tight catheter securing [8,9]. However, there is a lack of control groups in all these studies. A single centre retrospective and subsequent prospective audit found less complications when dialysis was initiated two weeks after Tenckhoff catheter insertion compared with immediate use [10].

Delay in starting PD results in the need for bridging HD in patients who require immediate dailysis. Bridging HD usually requires temporary HD catheters, with attendant risk of complications [11] and is also more expensive than PD [12].

Guideline bodies, such as Caring for Australasians with Renal Impairemnt (CARI) recommend, based on Level III and IV evidence, starting PD two weeks post Tenckhoff catheter insertion and advocate randomised controlled trials and further research [13]. International guidelines (European Dialysis and Transplant Association-European Renal Association and International Society for Peritoneal Dialysis, 1998 [14]) also suggest a two week delay and state that there is insufficient evidence to formulate a "guideline".

Comparing lag periods of one, two and four weeks after insertion of Tenckhoff catheters will enable us to determine how much effect the duration of the delay has, if any, on PD complications while determining any advantage that earlier start may have in terms of limiting HD during the bridging period.

### Aim

The primary purpose of this study is to find out the optimum time required to initiate PD after Tenckhoff catheter insertion. This will be done by measuring the incidence of PD complications in a period post PD commencement as well as the HD associated problems during the same period if bridging HD is performed.

## Methods/Design

### Study design

This is a randomised controlled trial to determine the optimal time to initiate PD after insertion of a Tenckhoff catheter.

Patient population: All patients undergoing PD catheter insertion at Royal Brisbane and Women's Hospital(RBWH) and Rockhampton Base Hospital (RBH), with the intention to use the catheter as soon as possible, will be invited to participate in the study.

Intervention: The interventions will comprise three groups. The first group will start PD at one week, the second group at two weeks and the third group at four weeks after the insertion of a Tenckhoff catheter.

### Setting

The Department of Renal Medicine, RBWH and RBH service populations of approximately 1.2 million and 200,000 respectively. This study is conducted by the 'Home Independent dialysis and Transition Program' (HITS) of the Department of Renal Medicine, RBWH and the Peritoneal Dialysis Service of RBH.

### Identification of eligible patients

Patients who satisfy the inclusion and exclusion criteria will be recruited from pre-dialysis clinics, PD clinics, catheter insertion preadmission clinics, catheter insertion operating lists and the HD population. Written informed consent will be obtained from all participants.

### Inclusion criteria

Male and female participants over 18 years of age, who will be receiving Continuous Ambulatory Peritoneal Dialysis (CAPD) or Automated Peritoneal Dialysis (APD) within four weeks of insertion of a PD catheter, will be eligible for this study.

### Exclusion criteria

Participants will be excluded if there is a history of psychological illness or condition which interferes with their ability to understand or comply with the requirements of the study or if they had an acute infectious episode in the last month before enrolment.

### Participants

Participants will be stratified by site and diabetic status. The patients will then be block randomised in equal proportions to the three treatment groups using randomly varying blocks of size three and six. The randomisation sequence was generated using Stata 11 software [15]. Group 1 will start dialysis one week after Tenckhoff catheter insertion, group 2 at two weeks and group 3 at four weeks. A research nurse independent of study nurses and physicians will undertake randomisation process.

Patients will initiate dialysis in equivalent fashion apart from the study variable of delay period before initiation. The patients will be trained by the PD nurses in their respective centres. The PD exit site and tunnel will be examined according to the usual clinical practice at each site to detect any complications. This will not interfere with routine dressing changes or reviews currently in practice.

### Outcome measures

#### Primary

Peritoneal fluid leaks (over the four weeks following start up of PD) and/or PD related infection - either exit site and/or tunnel and/or peritonitis - over the four weeks following start up of PD (Table 1).

**Table 1 T1:** Explanation of definitions to be used as part of this study

Terms	Definitions
Dialysate leak [17]	Exit-Site leak: Appearance of any moisture around the PD catheter that can be identified as dialysate (leak that contains a high glucose concentration, documented by a positive glucose dipstick of the leaking fluid)
	Dialysate leaks include not only those occurring around catheter but also dialysate loss from the peritoneal cavity, except that via the lumen of the PD catheter. If the diagnosis is uncertain Tenckhoffogram (intraperitoneal infusion of contrast material through the catheter with computed tomography) performed to confirm the anatomical leak[18]

Peritonitis [19]	Presence of two clinical signs and symptoms:
	• abdominal pain, nausea, vomiting, diarrhoea, fever and cloudy dialysate
	• Peritoneal dialysate WCC > 100/mm^3 ^with 50% neutrophils
	• Demonstration of bacteria on gram stain or culture

Exit site Infection (ESI)	Presence of purulent discharge or two of three of the following: erythema of >13 mm, induration and tenderness. Exit- site swab will be obtained in all suspected cases of ESI.

Tunnel Infection	Presence of two of three of the following: induration, tenderness, and radiographic evidence of a collection along the PD catheter tunnel.

#### Secondary

Composite of all PD catheter related complications and HD requirements and associated complications. PD catheter related complications include fluid leaks, infection, cuff erosion, cuff extrusion, failure to establish PD successfully (may be due to blockage, fibrin plug or outflow obstruction), delayed wound healing, haematoma, catheter revision or replacement, conversion to HD, HD related events, allergic reactions, hospitalisation for any reason with cause recorded as related to either surgery or start up of dialysis and death during the study period.

Outcomes will be recorded for eight weeks following the insertion of the Tenckhoff catheter. However, primary outcomes will relate only to those events occurring within four weeks after start up of dialysis as these will best inform the question of optimal delay time.

The HD related events include the number of HD treatments required during the study period, the use of temporary HD vascular access (non-tunnelled and tunnelled central venous catheters) and a composite of HD vascular access complications - infection (exit site or bacteraemia or septicaemia), blockage requiring intervention eg urokinase, replacement, repositioning and/or removal

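### Recording stops eight weeks after catheter insertion, so the four-week arm has no slack for a primary window that runs four weeks from PD start

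*Protocol article*

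**What the plan says.** Three statements in the protocol article bear on follow-up for the primary outcome.

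- **Recording period.** Under Outcome measures, Secondary: "Outcomes will be recorded for eight weeks following the insertion of the Tenckhoff catheter". The clock is insertion, and the sentence does not say which outcomes it covers.
- **Primary window.** Outcome measures, Primary, counts leaks and PD-related infection over four weeks from the start of PD, with no limit counted from insertion. The sentence after the recording rule repeats this: "primary outcomes will relate only to those events occurring within four weeks after start up of dialysis".
- **Start times.** Under Participants: "Group 1 will start dialysis one week after Tenckhoff catheter insertion, group 2 at two weeks and group 3 at four weeks".

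The Inclusion criteria admit patients expected to receive PD "within four weeks of insertion of a PD catheter, will be eligible for this study". The Data collection list includes "Date of PD catheter insertion and start of this period of peritoneal dialysis", so the real start date is known for each patient who begins. The article does not say what happens to primary recording when PD starts late.

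**The concern.** The end of recording is fixed from insertion and the primary window is fixed from PD start. Whether the first contains the second depends on when PD actually begins, and the room for delay differs by arm because the arms are defined by their start times.

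Group 3 is planned to start so that its window closes on the last day of recording. A Group 3 patient who starts one day late cannot have both an eight-week recording period and a complete four-week primary window. The same delay in Group 1 or 2 costs nothing. Late starts are foreseeable: the secondary outcomes include catheter revision, slow wound healing and inability to get PD going.

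The stake is an arm-dependent loss of primary follow-up. Missing events in Group 3 would lower the observed rate in the four-week arm, which the Discussion names as current practice at the main site, and would make the one- and two-week arms look relatively worse.

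**Working it through.** **Inputs**

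- Recording limit: 8 weeks = 56 days from insertion (Outcome measures, Secondary).
- Primary window: 4 weeks = 28 days from PD start (Outcome measures, Primary and Secondary).
- Planned starts: days 7, 14 and 28 (Participants).
- Expected complication rate 3%, non-inferiority margin 10 percentage points, 105 patients per group (Statistical considerations).
- Frequency and length of late starts: not given. All scenarios below are assumptions.

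**Step 1: the plan's own figure.** For Group 3, 28 + 28 = 56 days. Eight weeks is exactly what this arm needs if every start is on schedule.

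**Step 2: slack by arm.** Slack = 56 − (planned start + 28).

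| Group | Planned start | Window ends | Slack |
|---|---|---|---|
| 1 | day 7 | day 35 | 21 days |
| 2 | day 14 | day 42 | 14 days |
| 3 | day 28 | day 56 | 0 days |

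**Step 3: primary days recorded after a late start.** Recorded days = min(28, 56 − actual start day).

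| Days late | Group 1 | Group 2 | Group 3 |
|---|---|---|---|
| 0 | 28 | 28 | 28 |
| 1 | 28 | 28 | 27 |
| 3 | 28 | 28 | 25 |
| 7 | 28 | 28 | 21 |
| 14 | 28 | 28 | 14 |
| 21 | 28 | 21 | 7 |
| 28 | 21 | 14 | 0 |

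Up to 14 days late, only Group 3 loses days. Beyond that Group 2 is affected, and beyond 21 days Group 1 as well.

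**Step 4: size.** Assume the 3% risk is spread evenly over the 28 days. The loss for a patient d days late is then 3 × d/28 percentage points.

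- Whole of Group 3 late by 1, 3, 7 or 14 days: loss 0.11, 0.32, 0.75 or 1.50 points; recorded rate 2.89%, 2.68%, 2.25% or 1.50%.
- With a constant hazard instead, the recorded rate is 1 − 0.97^((28 − d)/28): 2.89%, 2.68%, 2.26% or 1.51%. The two assumptions agree closely.
- Only 10% to 50% of Group 3 late by 7 days: 0.10 × 0.75 = 0.075 points to 0.50 × 0.75 = 0.375 points. Among 105 patients that is 0.08 to 0.39 expected events.
- Starts scattered normally around day 28 with an assumed SD of 3 days: mean loss 3 × 0.399 = 1.2 days; 3 × 1.2/28 = 0.13 points.

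At a true rate of 3% the loss cannot exceed 3 points whatever the delays, and the margin is 10 points.

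**The case against.** **With starts on schedule nothing is lost.** This stands. All three windows are complete if PD begins as planned, and the eligibility wording makes a start after day 28 a departure from what was intended at entry. It is only an intention, however, and does not prevent slippage.

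**The eight-week sentence may govern secondary outcomes only.** It sits under that heading, the primary definition has no cap from insertion, and the next sentence puts the primary outcome on the PD-start clock. This reading is possible but not secure. The sentence speaks of outcomes without restriction, and the next one narrows which events count as primary without extending recording. A reader might infer that the two rules flatly contradict each other. The text supports less: they are unreconciled, and conflict only when a start is late.

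**Other arms can be truncated too.** This also stands. A reader might infer that only Group 3 can lose follow-up, but a start after day 28 shortens the window in any arm. What differs is the delay needed to get there.

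**The effect is small, and conservative for the trial's aim.** Both parts stand. A reader might infer that earlier starts are made to look worse by design, or that half of Group 3 would be truncated. The first does not follow, because punctual starts lose nothing. The second depends wholly on symmetric scatter around day 28, for which the article gives no basis.

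**Handling of late starts is a detail that an article leaves to the full protocol.** A tolerance around the start day would be such a detail. The point here is a recording rule that the article does state, and that does not fit the stated primary window once a Group 3 start slips.

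**Conclusion.** The point holds in limited form. As written, the recording rule leaves 21, 14 and 0 days of slack in Groups 1, 2 and 3, so any late start in Group 3 shortens its primary follow-up, while Groups 2 and 1 are affected only beyond 14 and 21 days. For delays of up to 14 days the loss is confined to the four-week arm. It lowers that arm's observed rate and so works against non-inferiority of the earlier starts.

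The slack figures rest on the document alone. The size rests on assumptions about late starts and on an even spread of the 3% risk. Losses of about 0.13 points (mean loss 1.2 days) to 0.75 points (whole arm 7 days late) would be unlikely to decide the trial against a 10-point margin. The case for acting is that the loss depends on arm, affects the primary outcome and costs almost nothing to avoid.

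**What to change.** Separate the two recording periods:

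- **Primary outcome.** State that leak, exit-site infection, tunnel infection and peritonitis are recorded for the full four weeks after the actual PD start date, even when this runs past eight weeks from insertion. The date is already collected.
- **Secondary outcomes.** Keep eight weeks from insertion for all arms. Extending every outcome to the later of the two dates would give late starters, mostly in Group 3, longer follow-up for HD treatments, access complications, hospitalisation and death, and would create a new imbalance.

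The cost is one sentence in the protocol and a few extra days of note review for late starters. No treatment or start time changes.
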